#### Covariates for Confounding Adjustment

Given the nonrandomized design, the following baseline covariates will be included in multivariable models and propensity score models: age, sex, GMFCS level, baseline GMFM-88 score, baseline MAS grade, and prior rehabilitation history.

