### Study Objective and Hypothesis

The primary objective of this study is to evaluate the clinical outcomes associated with a pediatric gait rehabilitation robot combined with rTMS in adolescents with spastic CP, compared with conventional rehabilitation therapy.

The primary hypothesis is that participants receiving robot-assisted gait training combined with rTMS may show greater improvements in gross motor function, gait performance, and muscle tone than those receiving conventional rehabilitation after 8 weeks of intervention. However, due to the observational design, causal inference is not possible. Specifically, changes in GMFM-88 scores from baseline to week 8 will serve as the primary end point. Secondary hypotheses are that the intervention group will exhibit superior improvements in 3D gait parameters, electromyography outcomes, and MAS scores at weeks 4 and 8.

Given the observational nature of the study, any observed between-group differences will be interpreted as associations rather than causal effects.

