## Methods

### Study Design

This study is designed as a prospective observational controlled study to evaluate the clinical outcomes associated with robotic gait training combined with rTMS in adolescents with spastic CP. An observational design was selected primarily because treatment allocation is influenced by family preference and clinical decision-making in real-world rehabilitation settings. In addition, the highly visible and technology-intensive nature of robotic rehabilitation limits the feasibility of participant and therapist blinding. Nevertheless, to minimize assessment bias, outcome evaluations will be conducted by independent rehabilitation physicians who are not involved in treatment delivery and are blinded to group allocation whenever feasible.

Eligible participants will be allocated to either an intervention group (robot-assisted gait training combined with rTMS) or a comparison group (conventional rehabilitation therapy) according to guardian preference after receiving standardized study information from a neutral research coordinator who is not involved in treatment administration or outcome assessment. Allocation decisions will be prospectively documented, and no randomization will be performed. Both groups will receive 5 treatment sessions per week over an 8-week intervention period. Clinical evaluations will be performed at baseline, week 4, and week 8 by trained rehabilitation physicians using standardized assessment procedures. The study flowchart is presented in Figure 1, and the schedule of enrollment, intervention, and assessment is summarized in Figure 2. This protocol was developed in accordance with the SPIRIT (Standard Protocol Items: Recommendations for Interventional Trials) guidelines and will be reported following the STROBE (Strengthening the Reporting of Observational Studies in Epidemiology) statement for observational studies [16,17]. Participant recruitment is scheduled to commence in January 2025, with data collection anticipated to be completed by December 2027.

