##### Gait Performance

Gait performance will be evaluated using a 3D gait analysis system [20]. Reflective markers will be placed at standardized anatomical landmarks, and both static and dynamic gait data will be collected according to institutional gait laboratory protocols.

Participants will perform repeated walking trials at self-selected walking speed along a standardized walkway. Key gait parameters will include gait cycle duration, cadence, stance and swing phase duration, step width, and step length.

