#### Propensity Score and Inverse Probability of Treatment Weighting

To further address confounding by indication, propensity score–based inverse probability of treatment weighting (IPTW) will be applied as a sensitivity analysis. Propensity scores will be estimated using a logistic regression model with group allocation as the dependent variable and the covariates listed above as predictors. After IPTW, balance will be assessed using SMDs, with an SMD<0.1 indicating acceptable balance. Covariate balance will be visualized using Love plots.

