## Results

This study was funded in 2024. Study recruitment began in January 2025 and as of June 2026, enrollment is ongoing; exact recruitment numbers are being verified with the research coordinator. This study has been approved by the ethics committee (YJ-2025-020-01) and supported by grants S2024094 and CDS2018Z005. Outcomes will be assessed at baseline, week 4, and week 8 via 3D gait analysis, electromyography, GMFM-88, MAS. Data collection is expected to be complete in December 2027, and the data will be analyzed with SPSS (IBM Corp). The results are expected to be published in spring 2028. All enrolled participants will undergo an 8-week intervention program consisting of 5 treatment sessions per week, with outcome assessments conducted at baseline, week 4, and week 8.

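### The covariate list carries the baselines of GMFM-88 and MAS but not those of the gait and nerve-conduction outcomes, which costs the secondary comparisons precision and some protection against regression to the mean

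*Protocol article*

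**What the plan says.** Under Covariates for Confounding Adjustment, the protocol article states that "the following baseline covariates will be included in multivariable models and propensity score models", and names six: "age, sex, GMFCS level, baseline GMFM-88 score, baseline MAS grade, and prior rehabilitation history". The sentence does not limit the list to the primary outcome. The section on the propensity score and inverse probability weighting (IPTW) reuses it, with "the covariates listed above as predictors", and adds that "balance will be assessed using SMDs, with an SMD<0.1 indicating acceptable balance".

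Allocation is not randomized. Participants enter a group "according to guardian preference after receiving standardized study information" (Study Design).

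The secondary hypotheses are that the intervention group will show "superior improvements in 3D gait parameters, electromyography outcomes, and MAS scores at weeks 4 and 8" (Study Objective and Hypothesis). The gait parameters are "gait cycle duration, cadence, stance and swing phase duration, step width, and step length" (Gait Performance). The electrophysiology outcomes are conduction velocity, latency and amplitude of three nerves (Electromyography Assessment). All are measured before treatment: "Outcomes will be assessed at baseline, week 4, and week 8 via 3D gait analysis, electromyography, GMFM-88, MAS" (Results).

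The mixed model under Primary Analysis is described for GMFM-88 only. The one analysis statement specific to the secondary outcomes is the false discovery rate correction.

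**The concern.** The list treats the outcomes unequally. It supplies an own-baseline term for the primary outcome and for one secondary outcome (MAS), but none for the other two secondary families. Followed as written, a model for cadence would adjust for baseline GMFM-88 and MAS but not for baseline cadence.

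Guardians choose for or against a gait robot, so walking ability before treatment could plausibly influence the choice, although the article does not say that it does. GMFCS level and GMFM-88 capture part of walking ability. There is less reason to expect them to stand in for nerve conduction. Because the propensity model uses the same six covariates, weighting does not target the gait and nerve baselines, and the balance check by implication does not cover them.

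Two things are at stake in the secondary comparisons:
- **Precision:** a measured predictor of the outcome goes unused as a covariate.
- **Bias:** subtracting the baseline does not remove regression to the mean if the groups differ at baseline.

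The false discovery rate correction addresses neither.

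**Working it through.** **1. The plan's own figure.** The article gives a sample size for the primary outcome only: d=0.60, two-sided alpha .05 and 80% power lead to 46 per group, and 54 after 15% attrition. A two-sample t test needs 44.6, that is 45 per group. 46/0.85 = 54.1. The stated figures reproduce within rounding, and this point does not change them. Power at 46 per group is 81.2%.

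**2. Inputs not in the document.** The article gives no SD, correlation, effect size or baseline imbalance for the gait or nerve outcomes. The following are therefore assumptions:
- correlation rho between baseline and follow-up, 0.5 to 0.9, with equal variance at both visits;
- d=0.60 borrowed from GMFM-88 as the standardized difference in change;
- 46 per group with the measurement;
- for the bias only, a difference d0 = 0.3 SD in the outcome's own baseline that remains after conditioning on the six listed covariates. For scale, the chance standard error of a baseline SMD at 46 per group is sqrt(2/46) = 0.21.

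**3. Precision.** In units of the single-visit variance, a change score has variance 2(1-rho). With the own baseline as a covariate the residual variance is 1-rho². The ratio is (1+rho)/2, so the effective d is 0.60/sqrt((1+rho)/2).

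| rho | variance ratio | effective d | power |
|---|---|---|---|
| no own-baseline term | 1 | 0.600 | 81.2% |
| 0.5 | 0.75 | 0.693 | 90.8% |
| 0.7 | 0.85 | 0.651 | 87.0% |
| 0.8 | 0.90 | 0.632 | 85.1% |
| 0.9 | 0.95 | 0.616 | 83.2% |

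If group and baseline are correlated, the gain shrinks. A 0.3 SD difference between equal groups inflates the variance by about 1 + 0.3²/4 = 1.0225, which lowers power to about 90%, 86% and 82% at rho 0.5, 0.7 and 0.9.

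**4. Bias of the change contrast.** Suppose there is no treatment effect and both groups regress to a common line, so that the expected follow-up value is rho times the baseline value. The change contrast is then off by -(1-rho) x d0. For d0 = 0.3 the absolute bias is 0.5 x 0.3 = 0.15 SD at rho 0.5, 0.3 x 0.3 = 0.09 SD at rho 0.7, and 0.1 x 0.3 = 0.03 SD at rho 0.9. The SD is that of the outcome at a single visit. The standard error of the contrast is sqrt(4(1-rho)/46), so the two-sided type I error is 11%, 8.6% and 6.2%, against a nominal 5%. Under this model, own-baseline adjustment removes the bias.

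**5. The reverse case.** Suppose instead that the groups have stable differences and parallel trends. The change contrast is then unbiased, and the own-baseline adjusted contrast is off by (1-rho) x d0 in the other direction: again 0.15, 0.09 and 0.03 SD.

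**The case against.** The strongest defense is that the article names no model for the secondary outcomes. The mixed model is stated for GMFM-88, the covariate section says what will be included rather than that nothing else may be, and a separate analysis plan is to be posted at the registry. An own-baseline term could sit there. That stands in part: nothing in the text rules the term out. But the article does not leave the covariates open. It names them for the models generally, with own baselines for GMFM-88 and MAS, and a reader who follows it leaves the others out.

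Three stronger readings are tempting, and the documents do not support them.

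- *The gait and nerve baselines go wholly unused.* The secondary hypotheses are worded as improvements, which implies a change or group-by-time contrast, and that subtracts the baseline.
- *Baseline differences carry over into week-8 values.* With d0 = 0.3 the carry-over would be rho x d0, or 0.15 to 0.27 SD over rho 0.5 to 0.9. It arises only if raw follow-up values are compared, and the article plans no such comparison.
- *The change contrast is biased, so own-baseline adjustment is the correct analysis.* In self-selected groups the two analyses rest on different assumptions, and step 5 shows that adjustment can itself introduce the bias.

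It is also fair to object to the sizes. The effect size was set for GMFM-88. The 81% is an unadjusted t test rather than a model with the six covariates. The alpha of .05 ignores the false discovery rate correction. Fewer than 46 per group may have gait data, since GMFCS I-V is eligible while gait is measured in walking trials. The figures show direction and rough scale. They do not forecast the power of any one endpoint. Finally, the article calls its findings hypothesis-generating and admits residual confounding. That limits the weight of the point. But the admission concerns unmeasured factors, and these baselines are measured.

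**Conclusion.** The point holds as an inexpensive improvement to the secondary analyses, mainly for precision and for checking balance. On the assumed inputs, the own-baseline term adds about 10 points of power at rho 0.5, 6 at 0.7 and 2 at 0.9, and slightly less if group and baseline are correlated. Its protection against regression to the mean is worth about 0.15 to 0.03 SD over the same range, on two conditions: a 0.3 SD baseline difference survives the listed covariates, and both groups regress to a common line. If the outcome is highly stable (rho near 0.9), both losses are small.

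A reader might infer that the main result is threatened. It is not: baseline GMFM-88 is on the list, and the primary analysis is unaffected.

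**What to change.** Add one sentence to Covariates for Confounding Adjustment, for example: *For each secondary outcome, the model for weeks 4 and 8 also includes the baseline value of that same outcome, in addition to the listed covariates, for participants with that measurement.*

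Alongside it:
- Leave the shared propensity model as it is. Some participants may have no gait baseline, and adding it there would affect the weighted analysis of every outcome.
- Report the SMD of each baseline gait and nerve measure before and after weighting.
- Keep the change contrast without the own-baseline term as a sensitivity analysis. If the two estimates differ, the result depends on whether common-line regression or parallel trends is assumed, and the report should say so.

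The cost is one or two extra parameters per secondary model and no new data collection. The statistical downside is the reverse bias of (1-rho) x imbalance under parallel trends, which the sensitivity analysis would expose. Enrollment was still under way in June 2026 and data collection runs to December 2027, so the change can be fixed before analysis.

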#### Propensity Score and Inverse Probability of Treatment Weighting

To further address confounding by indication, propensity score–based inverse probability of treatment weighting (IPTW) will be applied as a sensitivity analysis. Propensity scores will be estimated using a logistic regression model with group allocation as the dependent variable and the covariates listed above as predictors. After IPTW, balance will be assessed using SMDs, with an SMD<0.1 indicating acceptable balance. Covariate balance will be visualized using Love plots.

#### Missing Data Assumptions and Handling

Missing outcome data will be handled under the missing-at-random assumption using multiple imputation with 20 imputed datasets. Complete-case analysis will be conducted as a sensitivity analysis to assess the robustness of results under the missing-completely-at-random assumption. The primary analysis will use the intention-to-treat principle, including all enrolled participants with available baseline data.

#### Sensitivity Analyses

Sensitivity analyses will include (1) a per-protocol analysis excluding participants with attendance below 80%, as documented by standardized treatment attendance logs, and participants who received substantial additional rehabilitation therapies (defined as more than 3 rehabilitation sessions outside the study protocol during the intervention period); and (2) an IPTW-adjusted analysis based on propensity scores as described above.

#### Multiple Comparisons and Subgroup Analyses

False discovery rate correction will be applied to secondary outcomes to reduce type I error associated with multiple testing.

Exploratory subgroup analyses by GMFCS level (I-III vs IV-V) and age (13-15 vs 16-18 years) will be conducted using interaction terms.

### Ethical Considerations

This study will be conducted in accordance with the Declaration of Helsinki and has received approval from the ethics committee of China National Nuclear Corporation 416 Hospital (YJ-2025-020-01).

Written informed consent will be obtained from all participants and/or their legal guardians before enrollment. Participants and guardians will be informed of the study procedures, potential risks, and benefits, and their right to withdraw from the study at any time without consequences to future medical care. Participant confidentiality will be protected through coded identification and secure data storage. Study findings will be disseminated through peer-reviewed scientific journals and academic conferences.

## Results

This study was funded in 2024. Study recruitment began in January 2025 and as of June 2026, enrollment is ongoing; exact recruitment numbers are being verified with the research coordinator. This study has been approved by the ethics committee (YJ-2025-020-01) and supported by grants S2024094 and CDS2018Z005. Outcomes will be assessed at baseline, week 4, and week 8 via 3D gait analysis, electromyography, GMFM-88, MAS. Data collection is expected to be complete in December 2027, and the data will be analyzed with SPSS (IBM Corp). The results are expected to be published in spring 2028. All enrolled participants will undergo an 8-week intervention program consisting of 5 treatment sessions per week, with outcome assessments conducted at baseline, week 4, and week 8.

## Discussion

### Principal Rationale and Expected Contributions

This study aims to evaluate the clinical outcomes associated with pediatric gait rehabilitation robot-assisted training combined with rTMS in adolescents with spastic CP, compared with conventional rehabilitation therapy. Although both robotic gait training and rTMS have demonstrated potential benefits individually, evidence regarding their combined application in pediatric CP rehabilitation remains limited. Existing studies have suggested that robotic rehabilitation may improve gait biomechanics and motor learning through repetitive task-oriented training, while rTMS may facilitate cortical reorganization and enhance corticospinal excitability [21-23]. However, pediatric-specific protocols and multimodal intervention strategies remain insufficiently established.

The proposed intervention integrates peripheral motor training with central neuromodulation, providing a theoretically synergistic rehabilitation framework. Objective assessments, including 3D gait analysis, electromyography, GMFM-88, and MAS, are incorporated to provide a multidimensional evaluation of gait function, motor performance, and muscle tone.

### Interpretation Within the Context of Study Design

This study is designed as a prospective observational controlled study rather than a randomized controlled trial. Consequently, any between-group differences observed should be interpreted as associations rather than causal effects.

To reduce bias associated with nonrandom allocation, multivariable adjustment and propensity score–based methods will be used. Nevertheless, residual confounding due to unmeasured factors cannot be excluded.

Should the intervention group demonstrate superior outcomes, such findings would support the preliminary clinical value of the combined intervention and provide justification for future randomized controlled trials. Conversely, null findings would not necessarily exclude potential benefit but may suggest limited additional effectiveness within the current observational framework.

### Strengths and Limitations

Several strengths of this protocol should be acknowledged. First, the intervention combines robot-assisted gait rehabilitation with rTMS, targeting both peripheral motor execution and central neuroplastic modulation. Second, outcome assessment incorporates objective and multidimensional measures, including gait analysis and electrophysiological evaluation. Third, standardized intervention procedures and predefined statistical adjustment strategies have been incorporated to improve methodological rigor.

However, several limitations should also be recognized. First, the open-label nature of robotic rehabilitation limits participant and therapist blinding and may introduce performance bias. Although assessor blinding will be implemented whenever feasible, subjective assessments may still be influenced.

Second, the follow-up period is limited to 8 weeks. Given the chronic and developmental nature of CP, short-term outcomes may not fully capture sustained functional improvement. Future studies should incorporate longer-term follow-up assessments (eg, 6 or 12 months) to evaluate the durability of any observed improvements.

Third, participant heterogeneity, including differences in age, severity of motor impairment, and cognitive function, may influence treatment responsiveness.

Fourth, the age range of 13 to 18 years was selected primarily for device compatibility and developmental consistency. Consequently, findings may not be generalizable to younger children with CP.

Fifth, this study is conducted at a single tertiary rehabilitation center, which may limit generalizability. Multicenter studies are needed to validate the findings across diverse populations and clinical settings.

Finally, as an observational study, residual confounding and confounding by indication remain possible despite statistical adjustment. Furthermore, differences in intervention structure and treatment frequency between groups may partially influence observed outcomes.

### Comparison With Previous Research and Future Directions

Previous studies investigating rTMS or robotic rehabilitation in CP have primarily evaluated these modalities independently, with limited evidence regarding integrated intervention models. Additionally, stimulation parameters, training intensity, and intervention duration remain heterogeneous across studies, limiting comparability and standardization.

This study may contribute preliminary evidence regarding combined neuromodulation and robotic rehabilitation strategies and help inform future protocol optimization. Future research should prioritize multicenter randomized controlled trials, longer-term follow-up, and mechanistic investigations using neuroimaging and neurophysiological techniques. Integration with emerging technologies, such as virtual reality and biofeedback systems, may further enhance individualized rehabilitation approaches.

### Conclusions

This protocol describes a prospective observational study evaluating the clinical outcomes associated with robot-assisted pediatric gait rehabilitation training combined with rTMS in adolescents with spastic CP.

By integrating objective outcome assessment with multimodal rehabilitation intervention, this study is expected to provide preliminary evidence regarding the feasibility and potential clinical value of combining neuromodulation and robot-assisted therapy in pediatric rehabilitation.

Given the nonrandomized design, findings should be interpreted cautiously and viewed as hypothesis-generating rather than confirmatory. Future randomized and multicenter studies will be necessary to establish causality and optimize intervention strategies.

## Data Availability

Deidentified study data will be stored in a password-protected institutional repository of the Second Affiliated Hospital of Chengdu Medical College and will be available upon reasonable request to the corresponding author after study completion and primary publication. The study protocol and statistical analysis plan will be publicly available via the Chinese Clinical Trial Registry (ChiCTR2500105823).

